### Sample Size Determination

Considering that the research aims to test and compare 2 types of interventions (VR-facilitated exposure and yoga techniques), using a small sample population allows a detailed initial analysis and a rigorous evaluation of the mechanisms involved without requiring significant resources or large samples. In the exploratory phase, this type of study can identify important preliminary trends and effects, which can later be validated through larger studies. The study involves continuous monitoring of anxiety and other psychological and neurobiological parameters, which requires considerable resources for each participant. A small sample enables closer and more detailed tracking of each participant, ensuring higher-quality data collection and avoiding uncontrolled variables. The proposed interventions, such as yoga techniques and VR exposure, are complex and require specific preparation for each participant. Thus, a smaller population allows for more efficient adaptation of the intervention to individual needs and optimal program implementation. In addition, studies of this type often require costly equipment and expertise, such as VR hardware and certified yoga instructors. Therefore, limiting the sample population allows for efficient use of available resources while maintaining intervention quality. Finally, it is worth noting that previous studies have shown that both yoga and VR interventions can yield significant results with a limited number of sessions and participants. This suggests that a small sample may be sufficient to detect the desired psychological effects in the initial phase. Considering power analysis, 30 participants per group are required to detect significant differences regarding anxiety reduction with 80% power at a 5% significance level.

In psychological intervention research, particularly in RCTs involving novel therapeutic modalities such as VR-CBT and yoga, smaller sample sizes can be justified based on several methodological and practical considerations. First, exploratory trials with focused intervention designs often require fewer participants to detect meaningful preliminary effects, as observed in previous studies on VR-assisted exposure therapy and yoga-based interventions for anxiety [20]. In addition, studies incorporating intensive within-subject monitoring, such as repeated anxiety assessments over multiple sessions, benefit from smaller samples to enhance feasibility and ensure high-quality data collection without excessive resource expenditure [35]. Research also indicates that both VR-based cognitive interventions and yoga can yield significant results with as few as 20 to 30 participants per group, particularly when using highly targeted measures such as the STAI-Y1 or STAI-Y2, physiological markers, and emotion regulation scales [25,32]. Moreover, the personalized nature of interventions such as VR-CBT and structured yoga programs allows for greater within-group effect detection, reducing the need for large-scale samples compared to broad-spectrum behavioral health studies [31]. Given these considerations, the chosen sample size of 30 participants per intervention group aligns with previous RCTs demonstrating efficacy in VR and yoga-based anxiety interventions while maintaining statistical power at an optimal level for detecting significant differences in anxiety reduction [36]. This methodological approach ensures that while the study remains manageable in scale, it retains the rigor necessary to provide valuable insights into the comparative effectiveness of digital and holistic anxiety-reduction strategies.

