**Methods:**

A single-blinded randomized controlled trial will be conducted with 60 participants (n=30, 50% per intervention group) recruited from university and preuniversity counseling centers. The trial will measure whether the interventions reduce performance anxiety in students. Stratified randomization will be used to ensure equal distribution of baseline anxiety levels and gender across both groups. The primary outcome is a reduction in anxiety, measured using the State-Trait Anxiety Inventory-Y1 and State-Trait Anxiety Inventory-Y2 subscales. Secondary outcomes include emotional regulation and quality of life. Data will be collected at baseline, after the intervention, and during follow-up assessments. Statistical analyses will include parametric tests (eg, repeated-measures ANOVA and *t* tests) to compare anxiety reduction, emotional regulation, and quality of life across groups. The intention-to-treat approach will be applied to minimize bias due to participant dropouts. Sensitivity analyses will assess the robustness of the findings.

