### Goal of This Research

This research aims to evaluate and compare the effectiveness of 2 psychological intervention modalities—VR-facilitated exposure techniques based on cognitive behavioral intervention and yoga techniques involving body posture, breathing, and meditation—in reducing performance anxiety symptoms. In addition, the study seeks to investigate whether VR techniques lead to a more significant reduction in state anxiety, while yoga techniques are more effective in reducing trait anxiety.

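### The 30-per-group power claim names no difference to detect, leaves no room for the dropouts the protocol expects, and quotes one 5% level for two primary scales

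*Protocol article*

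**What the plan says.** The sample size section of the protocol article ends its first paragraph with the claim that "30 participants per group are required to detect significant differences regarding anxiety reduction with 80% power at a 5% significance level". It does not give the size of the difference, an SD, the sidedness, the test, or the scale.

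Four other places bear on that sentence:

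- **Number enrolled.** The Abstract (Methods) enrols 60 participants, 30 per intervention group. The number called required is therefore exactly the number randomised.
- **Primary outcome.** The same part of the Abstract states: "The primary outcome is a reduction in anxiety, measured using the State-Trait Anxiety Inventory-Y1 and State-Trait Anxiety Inventory-Y2 subscales". Goal of This Research gives each subscale its own hypothesis, in opposite directions: "whether VR techniques lead to a more significant reduction in state anxiety, while yoga techniques are more effective in reducing trait anxiety".
- **Dropout.** The Abstract and Data Analysis and Handling Missing Data both plan for dropouts, with intention-to-treat analysis, imputation and a per-protocol comparison. The VR and yoga intervention sections class participants who have not finished within one month as withdrawn or dropped out. No rate is given.
- **Justification.** The second paragraph of the sample size section argues that personalised interventions give a design that "allows for greater within-group effect detection, reducing the need for large-scale samples".

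**The concern.** A required sample size exists only relative to a stated difference, and a statistically significant difference is not one. As written, the claim cannot be checked. It also sits beside three statements that it does not fit.

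First, if 30 per group are needed, any loss of outcome data takes the trial below the claim, and the protocol expects loss. Second, one 80%/5% pair is quoted for a primary outcome made of two scales with two hypotheses. Third, the supporting argument concerns change within a group, while the trial's aim is the difference between groups. Large improvement in both arms, which the Results section anticipates, says nothing about power for the gap between them.

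Two readings of the results are at stake. A null comparison could be taken as evidence that the two active treatments perform alike, when a moderate difference could easily have been missed. A significant result on just one of the two scales could be taken as a 5%-level finding when the chance of at least one false positive is higher.

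**Working it through.** **Inputs from the protocol article.** 30 per arm, 80% power, 5% level (Sample Size Determination); 60 randomised 1:1 and two primary subscales (Abstract, Methods).

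**Assumptions, because the article gives no value.** Two-sided two-sample t test; dropout of 10% or 20% with completers analysed (27 or 24 per arm); correlation between the two test statistics from 0 to 0.8.

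**Step 1: the plan's own figure.** With no effect size or SD, 30 cannot be reproduced forwards. It can be solved backwards. With n analysed per arm, power is the probability that a noncentral t with 2n - 2 degrees of freedom and noncentrality d × √(n/2) exceeds the two-sided critical value.

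- For n = 30, α = 0.05 and power 0.80, d = 0.736, so the noncentrality is 0.736 × √15 = 2.85.
- Normal approximation: (1.960 + 0.842) × √(2/30) = 2.802 × 0.258 = 0.723.
- One-sided 5%: d = 0.650.

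Under the two-sided test, power with 30 per arm is 48% at 0.5 SD and 21% at 0.3 SD.

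**Step 2: dropout and two scales.** Power is shown at d = 0.736, together with the difference detectable at 80% power.

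| Analysed per arm | Power, α = 0.05 | Power, α = 0.025 | Detectable d, α = 0.05 | Detectable d, α = 0.025 |
|---|---|---|---|---|
| 30 | 80.0% | 70.7% | 0.736 | 0.814 |
| 27 (10% dropout) | 75.6% | 65.4% | 0.777 | 0.860 |
| 24 (20% dropout) | 70.4% | 59.4% | 0.826 | 0.915 |

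The 0.025 columns split 5% equally over the two scales. If 30 analysed per arm really are needed, the number to randomise is 30/0.9 = 33.3, so 34 per arm, at 10% dropout, and 30/0.8 = 37.5, so 38 per arm, at 20%.

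**Step 3: error rate with two tests at 5% each.** For independent tests, 1 - 0.95² = 9.75%. By simulation it is about 9.1% at correlation 0.5 and 7.8% at 0.8.

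**Step 4: requiring both scales to succeed.** By normal-approximation simulation at d = 0.736 on each scale, joint power is about 66% (correlation 0) to 74% (correlation 0.8).

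**Step 5: sensitivity to the choice of test.** Adjusting for baseline multiplies the detectable raw difference by √(1 - r²), where r is the pre-post correlation. At an assumed r = 0.5 this is 0.736 × √0.75 = 0.64 raw SD. A raw difference of 0.736 SD then behaves like 0.736/0.866 = 0.85, and power is 90%, 86% and 82% at α = 0.05 for 30, 27 and 24 per arm. At α = 0.025 it is 84%, 79% and 73%.

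**The case against.** The strongest reply is that nothing here proves an arithmetic error. With no inputs on the page there is no sum to falsify, and 0.74 SD is a back-calculation under a test the article does not name. The article is condensed, so the effect size may stand in a fuller document. All of that stands. A reader might infer that the trial has 80% power for 0.74 SD and nothing smaller. The documents do not support that: a one-sided test, or the covariate control and repeated-measures analyses mentioned under Data Analysis and Handling Missing Data, could detect less in raw SD. With baseline adjustment at r = 0.5, a raw difference of 0.736 SD keeps more than 80% power at the 5% level even after 20% dropout.

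A reader might also infer that the two scales will be tested without adjustment. The article states no adjustment, but it does not rule one out, and the rule may be in an analysis plan that is not shown. The point does not need that inference. An equal split costs power, two full-level tests raise the error rate, and requiring both scales lowers joint power. A fixed testing order would keep the 80%/5% pair for the first scale only. Nor does anything in the article make follow-up a co-primary test, so a further inflation over time points cannot be charged to the plan.

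The dropout rates are assumed, and imputation is planned. Imputation does not in general restore lost information, so this limits the size of the loss without removing it.

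Finally, the article calls the study exploratory and asks for larger trials later. That tempers how a null result should be read, but the same section also claims 80% power and an optimal level of power.

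**Conclusion.** The concern holds in a limited form. The mismatch is visible in the article itself: the number required equals the number randomised although dropouts are expected, one 5% level is quoted for two primary scales with separate hypotheses and no stated adjustment, and a within-group argument is used to support a between-arm comparison. The absent effect size and SD mean that the power claim cannot be verified as published.

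The size depends on the assumptions listed above. Under a two-sided two-sample t test, the claim implies about 0.74 SD or more between two active arms, on one scale, with all 60 analysed. At that difference the shortfall is roughly 4 to 10 percentage points of power from 10-20% dropout, 9 points from splitting the level, and 15 to 21 points from both together. If the level is not split, the family-wise error is 7.8-9.7% instead of 5%. Baseline adjustment with a useful pre-post correlation would offset much or all of the power loss, but the article does not tie its claim to such an analysis, and adjustment would leave the two-scale error rate untouched.

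**What to change.** 1. In Sample Size Determination, replace the claim with a statement of what 60 randomised participants can detect. For example: with an assumed 10-20% dropout (54 to 48 analysed), a two-sided two-sample t test has 80% power for a between-arm difference of 0.78-0.83 SD at 5%, or 0.86-0.92 SD at 2.5% per scale; smaller differences are not ruled out by a null result. If a baseline-adjusted analysis is intended, name it and give the assumed pre-post correlation.
2. Remove the within-group justification from the second paragraph of that section.
3. State how the overall 5% level is controlled across STAI-Y1 and STAI-Y2 for the primary between-arm comparison, for example by Holm.

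The choice of primary time point stays with the sponsor, since the protocol also hypothesises a long-term benefit of yoga.

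The cost is wording only, with no extra participants. The one downside is that the published figure looks less favourable than the present claim.

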### Screening

The enrollment form is designed to enable the selection of participants who meet the inclusion criteria and exclude those who do not meet the established research conditions. The introductory section of the form provides an overview of the research project and details the proposed program, including its duration, number of sessions, information about the research team and affiliated institutions, potential benefits in reducing anxiety, confirmation that the program is free, and clarification that there are no financial rewards. It also specifies the program’s purpose and how the research results will be used. Initially, we ensure that all respondents have read, understood, and agree with all the information provided in the introduction. The personal data section is followed by specific questions to determine eligibility for inclusion in or exclusion from the practice group. The first set of questions is designed to check alignment with the target age range and educational level (educational level, ongoing studies, the type of education, age, and financial level). The second set of questions assesses the mental and physical health of the participants and whether they are undergoing medication treatment or psychotherapy sessions, which are all essential considerations for inclusion in or exclusion from the research program. On the basis of the responses, those who meet the inclusion criteria will receive the initial evaluation test set.

### Instruments

#### Overview

First of all, participants will complete personal, medical, social, and demographic data sheets to identify aspects that make the volunteer incompatible with participation (ie, country of residence, county or region, gender or sex, level of education, educational attainment, current education, financial situation, marital status, profession, seniority in profession, level of responsibility in the workplace, and physical and psychiatric medical data, eg, current psychiatric diagnosis, undergoing medication, diagnosis of epilepsy, hearing or visual impairment, mobility difficulties, and spinal disorders).

#### Clinical Anxiety

Spielberger STAY-Y1 and STAY-Y2 subscales are used for the assessment of anxiety symptoms (the versions accredited by the Romanian College of Psychologists), which allow the identification of clinical symptoms of anxiety. The STAI (STAI-Y1 and STAI-Y2) [37,38] is a widely used instrument designed to measure both temporary anxiety (state) and general anxiety disposition (trait). The STAI-Y1 assesses state anxiety (situational emotional response), while the STAI-Y2 measures trait anxiety (general and enduring anxiety tendencies). The STAI has demonstrated high internal consistency (Cronbach α >0.90 for both subscales). It has been validated across multiple populations, including university students and patients with clinical anxiety. Extensive research supports its use in measuring performance-related anxiety and emotional dysregulation.

#### Performance Anxiety

The Academic Anxiety Inventory [39] is used for the assessment of performance anxiety manifestation, reflecting general patterns of anxiety related to examination situations or those related to solving specific academic tasks. Internal consistency is reported above 0.80, and construct validity has been demonstrated in studies linking cognitive interference, test anxiety, and academic performance [39].

#### Emotion Regulation Strategies

The Emotion Regulation Questionnaire [40] is a 10-item self-report scale measuring respondents’ tendency to regulate their emotions in two ways: (1) cognitive reinterpretation and (2) suppressing expression. We used a 7-point Likert-type scale ranging from 1 (strongly disagree) to 7 (strongly agree). Previous studies indicate good internal consistency, correlating well with measures of psychological well-being [41].

#### QoL Assessment

Tools will be used to assess the quality of the techniques used by assessing comfort or discomfort and the quality of psychoemotional support techniques. The QoL scale, through the QoL Inventory questionnaire, will be used.

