The participants will then start the psychoemotional support program and complete an anxiety level assessment at the end of each intervention session. At the end of the program, participants will complete the anxiety questionnaire again, along with an instrument assessing their comfort, discomfort, and the quality of the specific intervention techniques. To evaluate manifestations of performance anxiety, correlations between clinical anxiety and academic anxiety will be checked to indicate the strength and significance of their relationship. Details about the implementation of the techniques are presented in Table 1.

**Table 1 table1:** Overview of intervention components for virtual reality (VR)–assisted cognitive behavioral therapy (VR-CBT) and yoga-based interventions.

Intervention and phase		Session components	Duration

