**Yoga-based intervention**			
	Yoga practices (sessions 1-10)	Body postures (asanas), breathing techniques (pranayama), meditation, and relaxation exercises	60-90 min per session
	Final assessment (after the intervention)	QoLI, and self-report feedback on intervention experience	60 min

^a^QoLI: Quality of Life Inventory.

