### VR Cognitive Behavioral Intervention and Theoretical Background

The psychoemotional support intervention, facilitated by VR exposure techniques (6-10 sessions), uses Guided Meditation VR software and stand-alone Oculus Quest 2 and HTC Vive Flow hardware for alleviating performance anxiety. These consist of approximately 6 to 10 sessions of 20 to 30 minutes each of psychoemotional support based on cognitive behavioral techniques and integrative psychotherapy (with extension to a maximum of 1 h, if necessary). They will be carried out over a period of 2 weeks, up to a maximum of 1 month if it is not possible to organize the sessions in optimal conditions. After 1 month, the participants are reported as having withdrawn (in case of a request from the participants) or dropped out of the psychoemotional support program. The initial sessions (1-2 sessions) are designed for psychological assessment, psychoeducation, and familiarization with VR exposure techniques. In the next 2 to 3 sessions, different VR scenarios are tested to find a comfortable virtual environment for each patient. We test if patients agree that they are present in that generated virtual environment in a manner comparable to exposure in a natural environment (eg, a walk by the beach, in a forest, or an underwater itinerary). At this stage, subsequent exposure techniques will be developed using a combination of cognitive restructuring and relaxation methods, aimed at familiarizing participants with the technology and ensuring a pleasant experience. The next 1 to 2 sessions will continue with exercises already chosen, based on cognitive restructuring techniques combined with relaxation techniques. The last session is designed to review one of the exercises, assessing the quality of the technique and offering suggestions for improvement by going through a set of questions (eg, QoL through the QoL questionnaire). Each session concludes with a brief clinical assessment of anxiety using the State-Trait Anxiety Inventory (STAI) tool. Specific manifestations of performance anxiety are assessed.

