## Results

This study hypothesizes that the implementation of both VR techniques and yoga practices will yield a significant reduction in anxiety symptoms, as measured by the STAI-Y1 and STAI-Y2 scales. This study will start in the middle of the academic year in the fall of 2025 (to be relevant for performance anxiety) and will end in June 2026. It is anticipated that the VR group will experience a decrease in performance anxiety symptoms compared to the yoga group, which may require additional sessions. Concurrently, yoga sessions are expected to exert an intense impact with substantial psychoemotional rehabilitation effects. Furthermore, both interventions are predicted to lead to a meaningful enhancement in emotional regulation abilities, as assessed by the Emotion Regulation Questionnaire, with participants engaged in yoga anticipated to develop more effective cognitive reappraisal strategies. In assessing QoL, the use of the QoL Inventory among participants aims to reveal improvements, particularly in areas related to academic stress and examination-related anxiety, with both groups likely to report enhanced QoL after the intervention.

Comparative analyses between the 2 groups will highlight the specific outcomes associated with each technique. It is expected that the VR intervention may offer a more significant advantage in reducing acute anxiety symptoms, with rapid effects on stress perception. At the same time, the yoga group may sustain these effects over the long term by learning self-regulation methods. Neurobiological measurements are projected to provide evidence of favorable modifications in autonomic nervous system functioning, indicating beneficial biological responses to anxiety in both intervention groups. In addition, postintervention evaluations will reflect increased participant satisfaction with the techniques, particularly noting subjective differences in comfort and effectiveness. Yoga techniques are anticipated to be perceived as more relaxing, whereas VR may be seen as more stimulating.

In summary, the expected outcomes involve a reduction in anxiety symptoms, enhancement of life quality, and adaptation of emotional regulation strategies, underscoring the efficacy of both intervention methods in addressing performance anxiety among young individuals. This research may significantly contribute to the mental health field by providing relevant data for effective therapeutic strategies and new avenues of study.

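### The protocol does not clearly separate the quality-of-life measure from the rating of the techniques, and Table 1 has the arms complete the Quality of Life Inventory in different settings

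*Protocol article*

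**What the plan says.** The abstract (Methods) sets the role of the construct: "Secondary outcomes include emotional regulation and quality of life". The Results section ties it to an instrument: "In assessing QoL, the use of the QoL Inventory among participants aims to reveal improvements".

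Two places describe the QoL questionnaire differently.

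- Instruments, *QoL Assessment*, begins: "Tools will be used to assess the quality of the techniques used by assessing comfort or discomfort and the quality of psychoemotional support techniques". Its only other sentence is: "The QoL scale, through the QoL Inventory questionnaire, will be used".
- *VR Cognitive Behavioral Intervention and Theoretical Background* says that the last VR session is for "assessing the quality of the technique and offering suggestions for improvement by going through a set of questions (eg, QoL through the QoL questionnaire").

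Three places keep the two things apart.

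- Procedure, *Overview*, has participants repeat the anxiety questionnaire at the end of the programme "along with an instrument assessing their comfort, discomfort, and the quality of the specific intervention techniques". That instrument is not named and is not called the QoLI.
- Table 1, yoga arm, lists for the final assessment: "QoLI, and self-report feedback on intervention experience". For the VR arm, the QoLI is one of four items in session 9, after the review of a VR scenario and before debriefing and feedback.
- The Results section treats satisfaction with the techniques as an expected result of its own, apart from the QoLI.

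**The concern.** How good someone's life is and how good they found the technique are different quantities. If staff follow the VR description and the *QoL Assessment* text, participants may be handed the QoLI as part of giving their opinion of the programme. Some may then answer with the programme in mind.

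This matters for the comparison because the techniques differ by design, and the Results section already expects participants to perceive them differently: yoga as more relaxing, VR as more stimulating. A framing effect tied to the technique need not cancel between arms. The difference in setting in Table 1 adds to this, since only the VR arm meets the questionnaire inside a treatment session in which its own technique is being reviewed.

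**Working it through.** The point depends on no sample-size, power or error-rate figure, so no formula applies. The check sets the relevant sections side by side.

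1. **Which instrument carries the secondary outcome?** The abstract names the outcome and the Results section names the QoLI as its measure. These agree.

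2. **Is the same instrument given another job?** In the VR description, yes. The last session assesses technique quality through a set of questions, and the QoL questionnaire is the example given. This is the strongest evidence, because the link is made within one sentence. The *QoL Assessment* subsection is weaker. Its first sentence speaks of tools in the plural and does not name the QoLI; the connection comes from the heading and the sentence that follows. Still, the subsections on anxiety, academic anxiety and emotion regulation each state what their instrument measures. This one never says that the QoLI measures the participant's quality of life; the only purpose it states is rating the techniques.

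3. **Do other sections resolve it?** Only in part. The end-of-programme instrument in the Procedure can be read in two ways.
   - If it is the QoLI, the double use is confirmed.
   - If it is a different form, the constructs are separate, but that end-of-programme list then omits the QoL outcome, and the first sentence of *QoL Assessment* describes a form other than the one its heading announces.

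   Either reading leaves text to reconcile. Table 1 and the Results section favour the second.

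4. **Is the QoLI completed in the same setting in both arms?** Table 1 gives:
   - VR: within session 9, 20 to 30 minutes, together with scenario review, debriefing and feedback.
   - Yoga: in a final assessment after the intervention, 60 minutes, together with feedback on the experience.

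   Both arms pair the QoLI with feedback. They differ in that the VR arm completes it inside a treatment session that also goes back over a VR scenario, while the yoga arm completes it at a separate occasion.

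5. **How many participants are affected?** 30 + 30 = 60, that is, everyone randomised, on one of the two secondary outcomes named in the abstract. The document gives no QoLI items, scoring or expected scores, so neither the size nor the direction of any bias can be derived.

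**The case against.** The best opposing case is that this is loose wording. The first sentence of *QoL Assessment* does not mention the QoLI, and a natural reading is that two assessments share one heading. The Procedure, Table 1 and the Results section all list technique feedback or satisfaction apart from the QoLI. A fixed questionnaire asks what its items ask, whatever session it is given in. A journal article may also leave form order and instructions to the full protocol.

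Much of this stands. The mixing is not uniform, and leaving out item-level detail is no fault in an article. What remains is what the article does state: the VR description gives the QoL questionnaire as a means of judging the technique, and Table 1 fixes a different setting in each arm.

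Two stronger readings are tempting, and the document supports neither.

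- A reader might infer that the QoL result will in fact measure satisfaction with VR or yoga and cannot be interpreted as quality of life. Nothing says that technique ratings enter the QoLI score or that its instructions are changed. If the QoLI is a fixed questionnaire (an assumption), its score would not become a satisfaction score. The other gap would then be that technique quality has no named instrument.
- A reader might infer a third construct, academic anxiety, from the statement that "the use of the QoL Inventory among participants aims to reveal improvements, particularly in areas related to academic stress and examination-related anxiety". That sentence opens by referring to the assessment of QoL and is best read as a hypothesis about where quality of life may improve. Academic anxiety has its own inventory in the Instruments section, and the sentence needs no change.

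**Conclusion.** The concern holds in a limited form. The protocol does not clearly separate its quality-of-life measure from its measure of technique quality, and Table 1 places the QoLI in different settings in the two arms. As a result, a between-arm QoL difference, or the lack of one, would be harder to interpret. It would not be uninterpretable.

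The bias is possible, not demonstrated. It assumes that the purpose participants are given for a form, or the session in which they complete it, can colour their answers. The primary anxiety outcome is not touched by this point. It is worth correcting because a named secondary outcome is involved and the remedy is almost free.

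**What to change.** 1. Reconcile the *QoL Assessment* subsection and the VR intervention description with the Procedure, Table 1 and the Results section, so that all state the same purpose for the QoLI.
2. Reserve the QoLI for the participant's general quality of life. Have it self-completed with the same instructions and at the same post-intervention point in both arms, before and apart from scenario review, debriefing and feedback. Because Table 1 makes the VR review part of session 9, the text should say explicitly where that point falls in each arm.
3. Collect comfort, discomfort and technique quality afterwards, on the separate instrument already foreseen in the Procedure. Name that instrument and report it descriptively as acceptability.

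The cost is a change of wording and of the order of questionnaires. No construct is added and the sample size is unaffected. The change is best made before the first post-intervention assessments. If some have already taken place, the setting and order of the forms should be recorded for those participants.
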